#### Safety analyses

Adverse events (AEs) or serious adverse events (SAEs) will be recorded and coded to indicate the major event category but, as this is not a clinical trial of an investigational medicinal product, severity will not be graded. The frequency of all treatment-related AEs and SAEs recorded during the trial period will be displayed as the number of participants experiencing the AEs/SAEs, the percentage of participants and the number of AEs/SAEs will be presented both overall and by treatment arm.

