**Methods and analysis:**

This protocol describes a non-blinded, randomised feasibility trial with three parallel groups. The trial aims to recruit 90 participants (45 years or older) with a history of persistent knee pain consistent with a clinical diagnosis of knee osteoarthritis. Participants will be randomly assigned in a 1:1:1 allocation ratio. The ‘My Knee UK’ intervention arm will receive a self-directed unsupervised internet-based home exercise programme plus short message service support (targeting exercise behaviour change) for 12 weeks; the ‘Group E-Rehab’ intervention arm will receive group-based physiotherapist-prescribed home exercises delivered via videoconferencing accompanied by internet-interactive educational sessions for 12 weeks; the control arm will receive usual physiotherapy care or continue with their usual self-management (depending on their recruitment path). Feasibility variables, patient-reported outcomes and clinical findings measured at baseline, 3 and 9 months will be assessed and integrated with qualitative interview data from a subset of Group E-Rehab and My Knee UK participants. If considered feasible and acceptable, a definitive randomised controlled trial can be conducted to investigate the clinical effectiveness and cost-effectiveness of one or both interventions with a view to implementation in routine care.

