## Methods

### Trial design

This is an unblinded, single-centre, randomised feasibility trial with three parallel arms (two e-rehabilitation treatment arms and one control arm). The study protocol was designed to conform to the Standard Protocol Items: Recommendations for Interventional Trials guidelines^22 23^ and the extension of the Consolidated Standards of Reporting Trials (CONSORT) statement for randomised pilot and feasibility trials.^24^ The feasibility trial (phase II) opened to recruitment in March 2021 and the planned study end date is June 2023. Trial phases are outlined in figure 1.

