### Control arm

Participants allocated to the control group could receive any usual care intervention, ranging from no healthcare practitioner input to one or two physiotherapy sessions (delivered in-person or remotely by telephone or videoconferencing), to advice and guidance about self-management. The type of intervention that control group participants receive depends on their recruitment path.

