### Randomisation and blinding

Participants are randomised (by [name]) to one of the three groups using a 1:1:1 allocation ratio. Random allocation sequences with varying block length (3, 6 and 9), stratified by sex, are generated using an external password-protected web-based randomisation system (Sealed Envelope, London, UK). A dummy randomisation list,^33^ created using the same settings but different random seed number, was set up and then checked by the trial statistician ([name]) before the trial randomisation list was created.

The nature of this feasibility trial means it is not possible to blind participants, physiotherapists delivering the Group E-Rehab intervention or the study team managing the trial. However, the trial statistician will remain blinded to group allocation until all preliminary data checks have been performed at a blinded data review meeting and the database has been locked.

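### The only by-arm safety display that the protocol states is filtered on treatment-relatedness, which can be attributed unequally across the arms of this unblinded trial

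*Protocol article*

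**What the plan says.** The Safety analyses section of the protocol article takes two steps. The first concerns recording and has no relatedness condition: "Adverse events (AEs) or serious adverse events (SAEs) will be recorded and coded to indicate the major event category". It adds that "severity will not be graded". The second concerns display and does have such a condition: "The frequency of all treatment-related AEs and SAEs recorded during the trial period will be displayed". The display covers the number and percentage of participants with events and the number of events, which "will be presented both overall and by treatment arm".

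Two other parts of the article bear on how that condition works:

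- **Blinding.** Trial design states: "This is an unblinded, single-centre, randomised feasibility trial with three parallel arms". Randomisation and blinding adds that "it is not possible to blind participants, physiotherapists delivering the Group E-Rehab intervention or the study team managing the trial". Only the trial statistician is kept blind, until the database is locked.
- **Control arm.** What a control participant receives depends on the recruitment path. The Control arm section describes care "ranging from no healthcare practitioner input to one or two physiotherapy sessions", and also allows advice on self-management.

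**The concern.** A table by arm in a randomised trial will be read as a comparison, whether or not a test is attached to it. It is a fair comparison when events are counted by the same rule in every arm. Relatedness is a judgement made after randomisation, and it depends on what the participant received. In an exercise arm there is always a programme to which a knee flare or a fall might be attributed. For a control participant with no practitioner input, it is unclear what an event could be related to.

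If attribution differs by arm, the table can show an excess that does not exist, or hide one that does. Either would be a poor basis for describing the tolerability of the two programmes when a definitive trial is designed.

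**Working it through.** The safety section states no figure to reproduce. The check has a textual part and an illustrative part.

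**1. The text.** Recording is unfiltered and the stated display is filtered. The phrase can be read in two ways:
- Treatment-related qualifies both AEs and SAEs. Every row is then filtered.
- It qualifies AEs only, and all SAEs are shown. The SAE rows are then sound, but the AE rows, where non-serious flares and minor falls would appear, are still filtered.

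The AE rows depend on attribution under both readings.

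**2. Can attribution differ by arm?** Participants, the Group E-Rehab physiotherapists and the study team know the allocation. Keeping the statistician blind does not help if relatedness is already coded in the data. The control arm is mixed: some participants have physiotherapy or advice, and some may have no input. Nothing in the article makes attribution equal across arms.

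**3. Illustration.** The only input from the documents is 30 participants per arm (Sample size). The true risk *p* that a participant has an event, and the probabilities *a_I* and *a_C* that an event is called treatment-related in an intervention arm and in control, are assumptions. Each participant is counted once, and *p* is the same in both arms.

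- Expected number displayed in an arm = 30 × *p* × *a*
- Displayed difference = *p* × (*a_I* − *a_C*); true difference = 0

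With *p* = 20%, *a_I* = 50% and *a_C* = 10%: 30 × 0.20 × 0.50 = 3.0 against 30 × 0.20 × 0.10 = 0.6. The displayed difference is 0.20 × (0.50 − 0.10) = 8 percentage points.

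Over *p* from 10% to 30% and *a_I* from 30% to 80%:

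| Control attribution *a_C* | Smallest spurious difference | Largest spurious difference |
|---|---|---|
| 0 | 0.10 × 0.30 = 3 points | 0.30 × 0.80 = 24 points |
| 10% | 0.10 × 0.20 = 2 points | 0.30 × 0.70 = 21 points |
| 30% | 0.10 × 0 = 0 points | 0.30 × 0.50 = 15 points |

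The first row is a limiting case, because it treats every control participant as having nothing to which an event could be related. Suppose instead that a fraction *f* of controls has no input and zero attribution, and that the rest are attributed as in the intervention arm. The displayed difference is then *p* × *a_I* × *f*. With *p* = 20% and *a_I* = 50% it runs from 0 points (*f* = 0) to 10 points (*f* = 1). The documents do not give *f*.

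**4. The reverse direction.** Let the intervention arm have a true risk of 30% and control 20%. Suppose that flares in the exercise arm are largely put down to the underlying knee condition, so that 30% are attributed there against 50% in control. The table is expected to show 30 × 0.30 × 0.30 = 2.7 against 30 × 0.20 × 0.50 = 3.0. A true excess of 10 points appears as a deficit of 1 point.

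**5. Without the filter.** With equal risks of 10%, 20% or 30%, the expected counts are 3, 6 or 9 of 30 in every arm, and the difference is 0 whatever the attribution.

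**The case against.** The other side has several good points.

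- **The sentence is ambiguous and the SAP is not shown.** Its closing clause, on the number of events by arm, does not repeat the filter. Planned analyses refers to an SAP written before recruitment, which may contain an all-cause table. This stands as a caution. The article nevertheless states one display, and that display is filtered.
- **No decision depends on the table.** The analysis is descriptive, and safety is neither among the four success criteria nor in the rule for proceeding to a definitive trial. This stands, and it limits the weight of the point.
- **The illustrative inputs are assumed.** This stands. The calculation shows how the filter works, not how large the bias will be.

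A reader might also infer four stronger things that the article does not support:

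- *Control counts will be near zero whatever happens.* Some controls receive physiotherapy or advice, and Table 4 lists the control group under interventions with a variable duration of treatment. Events could be related to that care.
- *Relatedness is judged by unblinded people.* The article says who cannot be blinded. It does not say who judges relatedness.
- *This table is the only safety information.* WOMAC, global change, knee pain frequency and resource use, including contacts with health services, are scheduled at follow-up, and nothing shown limits them to particular arms. They carry information on worsening pain and use of care without any attribution.
- *There is no common point at which AEs are collected.* Table 4 has no AE row, but it is a condensed schedule and the questionnaires are not shown. Its silence is not evidence of a gap.

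**Conclusion.** The point holds in a limited form. The protocol records all AEs and SAEs, but the only by-arm display that it states depends on a relatedness judgement, for all events or at least for AEs. In an unblinded trial whose control arm ranges down to no practitioner input, that judgement can be made unequally across arms, so the displayed counts are not comparable. The direction of the bias is not fixed, and its size cannot be determined from the documents. The ranges above rest wholly on assumed risks and attribution rates. The consequence is a display that may mislead, not a wrong progression decision. The change is worth making because it is cheap and the events are already recorded.

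**What to change.** Reword the display rule so that all recorded AEs and SAEs are tabulated overall and by arm (participants, percentage, number of events) regardless of attribution, with treatment-related events shown as a subset row. This also removes the ambiguity over whether the filter covers SAEs. If the subset row is kept, a note on who judged relatedness, and on what counts as treatment for a control participant, would help the reader. The SAP may already cover this, in which case the protocol wording only needs to agree with it.

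No new data are needed. The cost is a longer table that includes events unrelated to the programmes.

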#### Qualitative study

Data derived from the participant and semistructured physiotherapist interviews will be transcribed verbatim. Transcripts will be analysed using framework analysis.^42^

### Feasibility trial outcome

Data from the feasibility trial and follow-up nested qualitative study will be integrated to support the case for determining whether one or both e-rehabilitation interventions are feasible, acceptable and have the potential to be implemented in practice. The qualitative and quantitative data will enable the potential for My Knee UK and/or Group E-Rehab to be introduced as alternative models of service delivery to be explored. The feasibility trial will be deemed successful if the results demonstrate that (1) participants and physiotherapists find one or both intervention(s) acceptable (using data from the nested qualitative study), (2) it is possible to calculate a manageable sample size for use in a definitive RCT, (3) attrition at visit 3 (3 months) is no more than 30% and (4) at least 40% of eligible patients are recruited to the trial. If one or both e-rehabilitation interventions are acceptable, the intention is to develop the protocol for and conduct a definitive RCT with a health economic component. This will be sufficiently powered for testing the wider use of My Knee UK and/or Group E-Rehab (depending on feasibility trial outcome) as a prescribed treatment for individuals with persistent knee pain.

## Discussion

The growing prevalence of persistent knee pain and OA requires the development and implementation of effective and accessible treatments that enable these patients to manage their symptoms. These treatments should be convenient for patients and should not overburden local MSK physiotherapy services. Current evidence suggests that for chronic conditions, such as OA, digital technologies can be used to deliver self-management programmes electronically.^9 43^

This trial aims to evaluate the feasibility and acceptability of two different e-rehabilitation interventions (Group E-Rehab and My Knee UK) in individuals with persistent knee pain. Education, advice about increasing general physical activity levels and strengthening exercises that can be tailored to individual needs are pivotal components of both interventions. Muscle strengthening programmes are beneficial in reducing pain and improving physical function in people with knee OA.^44^ In this trial, the home-based lower-limb strengthening exercise programme is either prescribed and monitored by a physiotherapist as a group-based intervention using videoconferencing (Group E-Rehab) or it is self-directed (accessed via the My Knee UK website). It is believed that the e-rehabilitation interventions under investigation in this trial will provide patients with access to the digital tools and resources needed for self-managing their knee pain and symptoms, and that one or both interventions could eventually be implemented within the NHS.

### Ethics and dissemination

This feasibility trial and current protocol (v.5.0, 25 January 2022) was approved by the West of Scotland Research Ethics Committee 5 (REC5), reference number 20/WS/0006 prior to commencing recruitment, which is ongoing. The study is sponsored by the University of Leeds (Research Integrity and Governance), UK and is registered with the ISRCTN (online supplemental 3). All individuals assisting with the trial will be informed of any protocol amendments, which will be approved by the Sponsor before being submitted to the REC/HRA for approval. The results will be disseminated to the study grant funder, submitted for publication in peer-reviewed journals and where requested, a summary of the study findings will be disseminated to study participants. No study participants will be identifiable in the study results.

10.1136/bmjopen-2022-063608.supp3Supplementary data
